## Abstract

**Background:**

Empowerment of hospital workers is known as a key factor of organizational performance and occupational health. Nevertheless, empowering workers remains a real challenge. As in many traditional organizations, hospitals follow a bureaucratic model defined by a managerial culture of control and a stratified organization, which at once weaken professionals’ mastery of their work and hinder their commitment and performance. Based on the existing literature this protocol describes a new managerial and organizational transformation program as well as the study design of its effect on worker empowerment in a large French public hospital. The project is funded by the French Ministry of Health for a total of 498,180 €.

**Methods:**

This study is a randomized controlled trial conducted in a French university hospital complex (CHU). The CHU comprises 12 sub-centers (SC) with about 20 care units and 1000 employees each. Randomization is performed at SC level. The intervention lasts 12 months and combines accompaniment of healthcare teams, frontline managers and SC directors to empower first-line professionals in the experimental SC. Quantitative outcome measurements are collected over 2 years during mandatory check-ups in the occupational medicine department. The primary outcomes are structural and psychological empowerment, motivational processes, managerial practices, working conditions, health and performance. Mixed linear modeling is the primary data analysis strategy.

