### Objectives

To assess the impact at one and 2 years of a standardised psychosocial intervention programme on the structural empowerment score in an “intervention SC”, in comparison with a “control SC”.To assess the impact of the intervention at one and 2 years on psychological empowerment scores.To detail the effects of the intervention on sub-dimensions of structural and psychological empowerment.To assess the effect of the intervention on motivational processes and factors.To assess the effect of the intervention on managerial practices.To assess the impact of the intervention on working conditions, health and performance.

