### Outcomes

The intervention aims to improve both the structural empowerment and the psychological empowerment of individuals. However, to determine the efficacy of the intervention, and also to understand any effects as accurately as possible, it appears worthwhile assessing conceptual network of empowerment in more global manner [44], here envisaged as predictors and outcomes of empowerment. These are listed in Table 1.

**Table 1 Tab1:** Key outcomes of the CHRYSALIDE study

Domain	Outcomes *(subdimensions)*	Instruments
Empowerment	Structural empowerment *(opportunity, support, information, resources)*	CWEQII, self-reported questionnaire [45]
	Psychological empowerment *(meaning, autonomy, skills, impact)*	PES, self-reported questionnaire [21]
Motivational processes	Basic psychological needs *(autonomy, competence, social affiliation)*	W-BNS, self-reported questionnaire [46, 47]
	Motivation *(intrinsic, identified, introjected, external motivations, lack of motivation)*	MWMS, self-reported questionnaire [48]
	Affective commitment	ACNC, self-reported questionnaire [49]
Working conditions	Empowering leadership *(delegation of authority, accountability, coaching for self-direction, information-sharing, skill development, coaching for innovation)*	LEBQ, self-reported questionnaire [50]
	Authentic leadership *(transparency, ethics, balanced processing, awareness)*	ALQ, self-reported questionnaire [51]
	Social support *(coworkers, supervisor, and institutional support)*	SPOS, self-reported questionnaire [52, 53]
	Distributive justice *(workload, salary, benefits, responsibilities)*	Organizational justice self-reported scale [54, 55]
	Global justice	Overall justice scale [56, 57]
	Work enrichment and design *(autonomy, feedback, significance, identity, variety of tasks)*	WDQF, self-reported questionnaire [58, 59]
	Role stressors *(role ambiguity, role conflicts)*	RCAS, self-reported questionnaire [60, 61]
	Illegitimate tasks *(unreasonable tasks, unnecessary tasks)*	BITS, self-reported questionnaire [62, 63]
	Quantitative workload	QWI, self-reported questionnaire [64]
	Satisfaction with work schedule	Adapted from usual satisfaction Likert scales [65, 66]
	Legal compliance of the work schedule	Institutional indicator collected by CHU
	Physical exertion at work	Borg 15 points Scale, assessment by practicioner [67]

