### Sample size

Our estimate is based on the effect observed by Dahinten (2014) on the overall score for structural empowerment. Given the hierarchical structure of the data in the present study, (“professional” level nested in the ‘“functional unit” level, in turn nested in the “department” level) an inflation factor needs to be applied to the standard calculation of sample size [78]. The calculation of the inflation factor is based on the following hypotheses:
an intra-class Correlation Coefficient (ICC) equal to 0.001 (within-SC correlation) We did not find any estimation in the literature of an ICC corresponding to our main judgement criterion and our study population. However ICC values are classically around 0.001 to 0.1 [79]an alpha risk of 5%a statistical power of 80%a difference of 0.12 points between global structural empowerment scores for professionals in the intervention group between T1 and T2 [42]a standard deviation of the global structural empowerment score of 0.56 points [42]

With these hypotheses, the number of professionals to include per group is 519. In all, 1038 professionals should be included. This expected number is close to the overall numbers of professionals in the two SCs. Given the considerable risk of loss to follow-up, the choice was to aim for an exhaustive coverage of the two SC, i.e. 600 to 700 individuals per group. We also rely on the compulsory nature of the check-up to reach this objective.

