### Statistical analysis

At the outset, the psychometric quality of the concepts measured in the questionnaires will be tested by exploratory and confirmatory factor analysis as well as an exploratory structural equation modelling. These analyses will enable the confirmation of the internal validity of the concepts postulated in the measurement scales and will, if needed, enable the adjustment or rejection of invalid in our sample. The analyses will be conducted under Mplus8 for Windows.

At the individual level, mixed linear models will used to assess the effects of the intervention on each outcome, while taking into account the hierarchical nature of the data, and possible variations in the implementation of the intervention protocol from one department or unit to another. The score of an outcome at T2 is thus explained by the fixed SC effect (intervention versus control) and by the random effect of the department or unit. A statistical adjustment will be made on the outcome score at T0 and on age, gender, profession, working time and size of the team, in line with the literature [36, 80]. The ICC will be estimated to have a precise idea of the effect of the department or unit.

Given the results obtained by Dahinten (2014), which showed a moderating effect of the level of implication at T0 on the impact of the intervention on implication at T1, a second model will be run each time including an interaction terms between the SC group and baseline measures of the outcome variable. These analyses should enable the identification of conditions that favour or undermine the interventions’ effect and implementation.

For the psychometric scales more particularly, the analyses will be performed on both the overall scores and the sub-dimension scores so as to refine the analysis of the effects as far as possible.

At the department and unit level, the score for each outcome will be calculated at T0 and T2 in each group. Mixed-effects linear models will be used to test the effects of the intervention over time, and between departments or units. These analyses will enable the study of variations in the effects of the intervention across the “intervention SC” departments or units.

The alpha risk retained for the statistical analysis is 5%. If the proportion of missing data exceeds 30%, multiple imputation will be considered.

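### The abstract makes seven outcomes or domains primary, but the trial is sized on the overall structural empowerment score alone, and no single primary time point is named

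*Protocol article*

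**What the plan says.** The Protocol article describes its outcomes in five places, and they do not agree.

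- **Abstract, Methods:** "The primary outcomes are structural and psychological empowerment, motivational processes, managerial practices, working conditions, health and performance". That is seven named constructs or domains, which together take in every domain of Table 1.
- **Objectives:** the first item is "To assess the impact at one and 2 years of a standardised psychosocial intervention programme on the structural empowerment score". Five further objectives follow. None is labelled primary or secondary, and no single time point is singled out.
- **Outcomes, Table 1:** headed "Key outcomes of the CHRYSALIDE study", with no ranking among its rows.
- **Sample size:** the effect is taken from an earlier study's result "on the overall score for structural empowerment". The text refers, in the singular, to "an ICC corresponding to our main judgement criterion and our study population".
- **Statistical analysis:** a mixed linear model is fitted for each outcome, with the T2 score as the response at the individual level. Psychometric scales are analysed as overall and sub-dimension scores, and a second model adds a group-by-baseline interaction. On the error rate: "The alpha risk retained for the statistical analysis is 5" per cent. Factor analyses are run first and may "enable the adjustment or rejection of invalid in our sample".

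**The concern.** A trial sized on one score cannot also have seven primary constructs or domains unless it says how they combine into a conclusion. The article does not say whether the intervention succeeds if structural empowerment improves, if any listed domain improves, or only if all do. The Discussion makes replication in other sub-centers depend on success, and the Background says the results are meant to guide public policy, so that definition carries weight.

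If the abstract is taken at its word, a significant result in any domain could be reported as a primary finding, with an error rate well above the stated 5%. If the sample size section is taken at its word, the abstract sentence is wrong. The time point is open in the same way: the objectives give two, the sample size uses a difference between T1 and T2, and the individual-level model uses T2.

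**Working it through.** **1. Reproduce the planned size from the single criterion.** Inputs from Sample size: difference 0.12, SD 0.56, alpha 5% (taken as two-sided), power 80%, ICC 0.001.

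- Before inflation: n0 = 2 × [0.56 × (1.960 + 0.842) / 0.12]² = 341.9 per group.
- With the whole sub-center as the cluster, the design effect is 1 + (n − 1) × 0.001. Solving for n gives n = n0 × (1 − 0.001) / (1 − 0.001 × n0) = 341.9 × 0.999 / 0.658 = 518.9, so 519.

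This matches the stated 519. The trial was sized for one test at 5%.

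**2. Size needed with more than one primary outcome.** Same inputs, assuming the same standardised effect for each outcome, 80% power for each, and alpha divided by k (Bonferroni).

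| k | alpha per test | n0 | n per group after inflation |
|---|---|---|---|
| 1 | 0.05 | 341.9 | 519 |
| 2 | 0.025 | 414.0 | about 706 |
| 7 | 0.0071 | 543.3 | about 1188 |
| 39 | 0.0013 | 718.5 | about 2550 |

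The planned 600 to 700 per group falls short even at k = 2, before any loss to follow-up.

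**3. Count the outcomes.** The abstract names 7. Table 1 has 2 (empowerment) + 3 (motivational) + 13 (working conditions) + 15 (health) + 6 (performance) = 39 rows. This is an upper count: medical history and a dependent relative at home look more like covariates.

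**4. Chance of at least one p < 0.05 when nothing is truly affected**, if every listed outcome is primary and each is tested at 5%.

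- Independent tests: 1 − 0.95^7 = 30.2%; 1 − 0.95^39 = 86.5%.
- Correlated tests: the documents give no correlations, so a common correlation ρ between test statistics is assumed. With c = 1.960, the rate is 1 − ∫ [Φ((c − √ρ·u)/√(1−ρ)) − Φ((−c − √ρ·u)/√(1−ρ))]^k φ(u) du.

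| k | ρ = 0 | ρ = 0.3 | ρ = 0.5 | ρ = 0.7 |
|---|---|---|---|---|
| 7 | 30.2% | 27.1% | 23.0% | 17.8% |
| 39 | 86.5% | 73.8% | 56.6% | 37.2% |

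Counting only results that favour the intervention (2.5% each), the 39-row figures fall to 62.7% if independent and 28.6% at ρ = 0.5.

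**The case against.** The strongest reply is that the body of the article already identifies the main criterion. Structural empowerment is the first objective and the only score used for sizing, and the individual-level model specifies T2. On that view the abstract contains one loose sentence. Much of this stands, and it is why the repair is simple. But the objectives are unranked, they give two time points, and the abstract says the opposite in plain words.

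Several stronger readings are tempting and are not supported:

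- **That a chance success is close to certain.** This needs nearly independent tests and every sub-dimension counted as primary. Many of the outcomes are self-report scales from the same people, so positive correlation is likely.
- **That about 200 primary tests are planned.** Adding all 65 listed sub-items and doubling for the second model gives (39 + 65) × 2 = 208. Only 45 of the 65 belong to psychometric scales, to which the sub-dimension analysis is mainly directed. The interaction models study moderation, and nothing calls them primary.
- **That multiplicity control is absent.** The article states an overall alpha of 5%. It does not say that each test uses 5% unadjusted, and a procedure may sit in an analysis plan that is not shown. The finding is the contradiction over what is primary.
- **That the main scale will be rescored after results are known.** The factor analyses come at the start, and no wave is stated. Nothing says the structural empowerment score will change. This calls only for a clarifying sentence.
- **That the registry entry is also wrong.** It is not among the documents, so nothing can be said about it.

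It can also be said that psychological empowerment is a joint aim of the intervention and could be co-primary. That is a legitimate design, but the article would then have to state the success rule, and the present sample size does not cover a Bonferroni split over two.

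**Conclusion.** The concern holds as an internal contradiction. The abstract and the sample size section name different primary sets, and the objectives and analysis leave the primary time point open. The planned size supports one primary test and falls short of a Bonferroni split over two.

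The error rates in the working are conditional. They assume that the abstract's list is taken literally, that each outcome is tested at an unadjusted 5%, and that each test holds its nominal level. The correlations are assumptions. Within those limits the inflation over 5% is substantial, about 18% to 30% for seven tests and 37% to 87% for 39, but it is not near-certainty. The sample size figures take the plan's own difference, SD and ICC as given.

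**What to change.** Reconcile the abstract, Objectives, Sample size and Statistical analysis sections:

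1. Name the overall structural empowerment score at one stated time point as the single primary outcome. T2 is the natural choice because the individual-level model already uses it.
2. Label psychological empowerment and all other scores, sub-dimensions and interaction models secondary or exploratory, and correct the abstract sentence to match.
3. State that the scoring of the primary scale is fixed before follow-up data are analysed by group.

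The cost is a few sentences. The 519 per group stands, since it was calculated for this one score. The real downside is that results in the other domains, including psychological empowerment, can no longer be claimed as primary findings.

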**Discussion:**

The protocol was approved by the CHU health ethics committee. The results of the analysis of the intervention effects will be reported in a series of scientific articles. The results will contribute to reflection on prevention and management policies, and to the development of Workplace Quality-of-Life. If the intervention is a success, the system will warrant replication in other SCs and in other health facilities.

**Trial registration:**

The study was retrospectively registered at ClinicalTrials.gov on July 4, 2019 (NCT04010773).

## Background

As in many other countries, the French health system has been under constant pressure to control its medical expenditure [1–3], which has favoured styles of hospital management that are mainly focused on economic aspects. However, over recent years, empirical evidence [4–7] has emerged, alongside questioning in the managerial spheres [8], on the interconnections between quality-of-life in the workplace, care quality and economic performances. In this perspective, the *Haute Autorité de la Santé* (HAS, French health authority) is today clearly encouraging the piloting of hospital performances by way of workplace quality-of-life (W-QoL) [9]. In this respect, the HAS [8] chooses to define W-QoL not as a collection of dimensions reflecting an optimal state of health, but rather as a participatory organisational approach: ‘This promotes the notion that the perceptions entertained by staff on W-QoL depend on their ability to put their job content into words and act on that content. It is in favour of a role of the staff and their representatives as players in the construction of solutions, in particular in the organisational field, alongside the management, the administration and experts’ (p.35).

This redefinition of W-QoL recalls research in the field of psychology [10–12] and management [13–16] on the theme of empowerment. Giving more latitude and support to collectives in the definition of their work increases the levels of identification and implication, which in turn favours performance and wellbeing. However the ethnographic literature shows that an evolution of this nature entails a radical cultural and structural shift, because it questions the distribution of power within a health facility and the representation that each protagonist (manager, administration, doctors, nurses etc.) has of his or her role [17–20].

This raises two questions: 1) how can organisations be accompanied in achieving this structural and cultural transformation? And 2) how can the impact of an accompaniment of this sort towards this new conception of W-QoL be measured? Whether in providing a theoretical basis for the intervention, or in operationalising the assessment and measurement of these processes, the models of structural empowerment and psychological empowerment have been taken up in north America as relevant paradigms.

Since the early days, in the 1970s and 1980s, empowerment has been seen as a multi-level concept [6, 10, 11]. On the individual level, Thomas & Velthouse (1990), [15, 16, 21] conceptualised psychological empowerment as the creation of a system of cognitions (beliefs and attitudes) based on experience (and its subjective interpretation), which can be likened to systems of expectations of an individual in relation to his or her abilities, level of implication and performances, and this in turn is predictive of attitudes and behaviours such as commitment to the job and actual performance. This involves the belief entertained by an individual that he/she 1) has an impact on the professional environment, 2) that he/she possesses the required professional skills, 3) that his/her professional actions are the result of his or her own will-power, and 4) that his/her work has meaning.

On the environmental level, structural empowerment [14, 22] for its part relates to the social, physical and organisational components of the environment that favour, predict or mediate the influence, control or power of social actors. Here the issues are access to 1) opportunities for professional development, 2) relevant information on the enterprise and its strategies, 3) adequate support to enable and contribute to personal development, and 4) the possibility of exerting an influence to obtain more resources (funds, equipment, human resources).

The effects of psychological [23] and structural empowerment in care facilities have been widely studied in the literature. Whatever the level of implementation, favourable effects are observed on job satisfaction [24–27], caregiver health [25, 28–31], the intention to stay in the facility [30, 32, 33], commitment [24, 34, 35], innovation [16, 21, 36], management efficiency [16], implication in unplanned pro-organisational behaviours [31, 37], care quality [4, 38, 39], and performance generally [4, 37]. The psychological and structural levels of empowerment are thus relevant intervention targets, liable to achieve an overall improvement in the performances of care facilities.

To our knowledge, there are six controlled interventional studies in care environments that have targeted empowerment among first-line professionals.

Four of these studies targeted interventions among individuals. In each case, volunteering subjects were included in groups distinct from their respective work teams, and they were asked to exchange their experiences and practices in the presence of a facilitator, for the purpose of fostering empowerment. Three of these interventions presented positive effects on psychological empowerment among the participants. They did not however demonstrate any effect on structural empowerment [40] nor on job satisfaction [40, 41]. These results show that it is worth collectively supporting elaborations by individuals on the determinants of their experiences and the identification of solutions, so as to foster psychological empowerment. But at the same times these studies point to the limitations of this type of intervention, which does not have any effect on access to empowerment structures via team processes, and management or organisation adjustments.

McPhee, Dahinten et al. (2013, 2014), [34, 42] developed a training and back-up protocol centred on front-line managers, aiming to promote pro-empowerment managerial practices. The study evidenced a positive effect on team implication at 1 year, partially mediated by structural empowerment. However, this intervention did not appear to improve psychological empowerment among caregivers, nor did it improve commitment among disengaged professionals. Yet the literature shows that psychological empowerment is the precursor of the internalisation of motivation and implication [12, 15]. In this perspective, in the absence of psychological empowerment, participants would not be able to internalise the values associated with the job and enhance their level of implication, while those who already identify with their jobs would increase their implication. Thus, although this study genuinely demonstrates the value of interventions at management level, it also shows the limitations of this mode of intervention for psychological empowerment, and *in fine* for the actual commitment of professionals.

In another study by Laschinger et al. (2012) [43], teams and their front-line supervisor were directly implicated in a process of collective problem-solving with the support of a facilitator. The managerial staff had the support of a chief nursing officer. The intervention improved structural empowerment at 6 months (psychological empowerment was not assessed). However, access to information and opportunities was not improved. Access to these empowerment structures clearly involves protagonists and areas of action outside the care team. For instance, access to opportunities requires human resources in the area of careers, mobility, training and administrative rules for promotion. Access to information also involves different facility management structures and their ability to communicate and transfer information to healthcare teams concerning the situation of the hospital, its values and its objectives. In this perspective, it can be postulated that focusing on healthcare teams and their local management, with the support of only a chief nursing officer, restricts the scope for action of a more structural nature by the management (general director, human resource director, Chief medical officer, and other types of management), despite the fact that these protagonists contribute to defining professionals’ access to empowerment structures.

In view of all these political, theoretical and empirical elements (e.g., ethnographical, experimental), the present study was designed to test the efficacy of a new intervention model combining an accompaniment of healthcare teams, training and accompaniment of front-line managers and top managers (directors), for the purpose of enhancing the powers of first-line professionals.

The design is an experimental randomised controlled study on the effect of an intervention in a university hospital Sub-Centre (the “intervention SC”) compared to a “control SC”, within a large French university hospital complex (*Centre Hospitalier Universitaire*, CHU) with more than 12,000 salaried staff.

The project is called CHRYSALIDE. It is funded on call for scientific tender by the French ministry of health for total of 498,180 €. The results of this research are intended to orient future public policies in the areas of prevention and health facility management.

This article describes the study protocol and includes a description of the intervention and the quantitative methods used to assess its effects. The study was planned to start in January 2017, recruitment of participants began in 2018 for the baseline, and the data collection is to be complete in summer 2020.

